**Fig. 5 Fig5:**
[figure not shown]
Example of the measurement of T2 values. The regenerative cartilage in this case is located in the medial femoral condyle. **a** Shows the T2 value of regenerative cartilage. **b** Shows the T2 value of normal control cartilage. The color in the region of interest indicates the T2 value

T2 mapping is a functional index to evaluate the composition of articular cartilage. The spatial distribution of T2 indicates the water and collagen content and improvement of the direction, which is beneficial for the objective and dynamic monitoring of the regenerated cartilage. The T2 value of the cartilage is an important indicator to measure the structural integrity of collagen fibers, based on which, we can dynamically detect the biochemical properties and maturation process of the repaired tissues.

#### In vivo evaluation of regenerative cartilage with △R1 value

Delayed Gadolinium-enhanced Magnetic Resonance Imaging of Cartilage (dGEMRIC) is an imaging technique that indirectly reflects joint cartilage glycosaminoglycan (GAG) content based on the ion distribution of fixed charge density (FCD) (Fig. 6). GAG molecules with negatively charged hydroxyl and sulfate groups indicate cartilage FCD. Gd-DTPA^2−^, an MRI contrast agent, is also negatively charged, and its distribution in the cartilage is negatively correlated with FCD; therefore, there is a negative correlation between Gd-DTPA^2−^ distribution and GAG content. △*R1* = 1/*T1*post−1/*T1*pre. Higher GAG content is accompanied by gradually reduced △*R1* values, which is used to determine regeneration of the regenerated cartilage [21].

**Fig. 6 Fig6:**
[figure not shown]
Example of the measurement of T1 values. The regenerative cartilage in this case is located on the patella. **a** Shows the T1 value of regenerative cartilage. **b** Shows the T1 value of normal control cartilage. The color in the region of interest reflects the T1 value

### Outcome measures

#### Primary outcome measure

The Lysholm score for efficacy evaluation will be recorded at 12 months postoperatively. The Lysholm score [22] ranges from 0–100 points and consists of eight dimensions: a score of 80–100 points indicates elimination of all or the main symptoms, basic recovery of joint function, being capable of participating in normal labor and work (excellent); 60–79 points indicates elimination of all or the main symptoms, basic recovery or great improvement in the main function of the joint (good); and 0–59 points indicates no symptom improvement or symptom deterioration (poor). Efficiency = the number of excellent and good cases/the total number of cases × 100%.

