### Statistical analysis

Data will be analyzed using SPSS19.0 software (IBM Corp., Armonk, NY, USA). A statistical significance level of 0.05 will be used. Normally distributed data will be expressed as the mean ± standard deviation, and non-normally distributed data will be expressed as the median, minimum, and maximum. Classified variables will be expressed as a number and percentage.

The analysis will be performed on the basis of the intent-to-treat principle. A full analysis set following the principle of intent-to-treat will consist of a data set for all patients who participated in the trial, regardless of compliance or withdrawal. For patients who are lost to follow-up, the missing data will be imputed by the last-observation-carried-forward method based on the final observed value.

Descriptive statistics will be used for baseline feature data. Pearson’s chi-squared test or Fisher’s exact test will be used for intergroup comparisons of categorical variables, such as curative outcomes and postoperative incidence of adverse events. For independent variables, such as IKDC score, VAS score, T2 value, and △*R1*, an independent sample *t* test or the Mann-Whitney *U* test will be used.

A multivariate logistic regression analysis model will be used to adjust for possible confounding variables such as age, sex, etiology, cartilage defect area, meniscus injury, course of disease, severity of cartilage injury, postoperative complications, and surgeon (experience).

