## Appendix

**Table 2 Tab2:** Lysholm score sheet

Lysholm score			Left knee	Right knee
Claudication (5 points)	No 5	5		
	Mild or periodically 3	3		
Need support (5 points)	No 5	5		
	Cane or crutch 2	2		
	Cannot bear 0	0		
Angina (15 points)	No 15	15		
	Snagging without pain 10	10		
	Occasional angina 6	6		
	Frequent angina 2	2		
	Joint angina 0	0		
Joint instability (25 points)	No 25	25		
	Rarely 20	20		
	Frequently in heavy exercise 15	15		
	Occasional in daily life 10	10		
	Frequent in daily life 5	5		
	Each step 0	0		
Pain (25 points)	No	25		
	Rarely	20		
	Obvious during heavy exercise	15		
	Obvious after 2 km walking	10		
	Obvious within 2 km walking	5		
	Continuous	0		
Swelling (10 points)	No	10		
	Heavy exercise	6		
	Daily exercise	2		
	Continuous	0		
Stairs (10 points)	No	10		
	Mild difficulty	6		
	One step	2		
Squatting (5 points)	No	5		
	Mild difficulty	4		
	Less than 90°	2		
	Cannot	0		
		Total		

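### The primary 12-month Lysholm score is cut to a 60-or-more rate with no baseline term, which loses a substantial part of its information and gives labels that the protocol's own score sheet can contradict

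*Protocol article*

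**What the plan says.** **Objective and outcome.** Under Study objectives, functional and symptomatic recovery is to be compared through Lysholm scores at 12 months. Primary outcome measure begins in the same way: "The Lysholm score for efficacy evaluation will be recorded at 12 months postoperatively". It then splits the 0–100 scale into three bands (80–100 excellent, 60–79 good, 0–59 poor). The middle band reads "60–79 points indicates elimination of all or the main symptoms, basic recovery or great improvement in the main function of the joint (good" and the lowest reads "0–59 points indicates no symptom improvement or symptom deterioration (poor". The summary measure is "Efficiency = the number of excellent and good cases/the total number of cases", so a success is any score of 60 or more.

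**Sample size.** The calculation uses this rate: 78% for microfracture and 97% for the graft, two-sided α of 0.05, 80% power, 84 patients, and 50 per group after allowing for 20% dropout.

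**Statistical analysis.** Curative outcomes are compared by Pearson's chi-squared or Fisher's exact test, with a logistic model for adjustment. The sentence on score comparisons opens "For independent variables, such as IKDC score, VAS score, T2 value" and does not name Lysholm. Baseline Lysholm is not among the named adjustment variables.

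**Baseline.** Secondary outcome measures lists the Lysholm score at baseline, 3, 6 and 18 months, so baseline is collected. The inclusion and exclusion criteria set no upper limit on it.

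**Score sheet (Appendix, Table 2).** Two items carry a quarter of the total each: "Pain (25 points" and "Joint instability (25 points". The worst option on each (continuous pain; instability at each step) scores 0.

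**The concern.** Two things follow from the cut.

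The first is lost information. A 0–100 score becomes a yes/no result, and the cut lies well down the expected distribution, since 78% of controls are assumed to pass it. Only patients in the lower tail can then separate the arms; a shift from, say, 65 to 85 contributes nothing. If the true benefit is smaller than the assumed 19 percentage points, the rate comparison may miss a functional gain that the score would show.

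The second is meaning. The bands are worded as improvement and symptom elimination, but they are assigned from one 12-month total. A total does not show which symptoms remain, and a single time point cannot show change. A reported efficiency could therefore be read as recovery when it means only a total of at least 60.

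**Working it through.** **1. The plan's own figure.** Inputs from Sample size: p₁ = 0.78, p₂ = 0.97, two-sided α = 0.05, power 80%, so (1.960 + 0.842)² = 7.849. With H(p) = −p ln p − (1−p) ln(1−p), the likelihood-ratio formula uses g = 2[H(0.875) − (H(0.78) + H(0.97))/2] = 0.0919. Total N = 7.849/0.0919 = 85.4, rounded to 86 and within two patients of the stated 84. The usual pooled formula gives 94. The planned 42 per arm is used below as the comparator; 50 × 0.8 = 40 per arm are expected to remain after dropout.

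**2. Score analysis, normal model (assumption: equal SDs).** The rates imply a shift of z(0.97) − z(0.78) = 1.881 − 0.772 = 1.109 SD.
- Normal formula: n = 2 × 7.849/1.109² = 12.8, so 13 per arm; the exact t test needs 14.
- Against 42: 1 − 13/42 = 69%; 1 − 14/42 = 67%. The loss is about two thirds.

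**3. Score analysis, skewed models (assumption).** Let the deficit (100 − score) follow a gamma distribution, scaled so that 78% and 97% of patients have a deficit of 40 or less. Per arm, n = (SD₁² + SD₂²) × 7.849/(mean difference)².

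| Gamma shape | Means (control, graft) | SDs (control, graft) | n per arm | Loss against 42 |
|---|---|---|---|---|
| 1 | 73.6, 88.6 | 26.4, 11.4 | 28.8 | 31% |
| 1.5 | 72.8, 86.6 | 22.2, 11.0 | 25.4 | 40% |
| 2 | 72.1, 85.1 | 19.7, 10.6 | 23.4 | 44% |
| 3 | 70.9, 82.8 | 16.8, 9.9 | 21.1 | 50% |

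**4. Which model is plausible.** Under the normal model the graft-arm mean is 60 + 1.881 × SD. At an assumed SD of 15 that is 88.2, with 22% of patients above the maximum of 100. At SD 20 it is 97.6, with 45% above 100. Only a small SD, near 10, makes the model workable, so the skewed range deserves more weight.

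**5. Power at 40 per arm, normal model only.**

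| True effect | t test on the score | Fisher on the rate | Pearson on the rate |
|---|---|---|---|
| 1.11 SD (78% v 97%) | 99.8% | 65.8% | 81.1% |
| 0.6 SD (78% v 91.5%) | 75.5% | 29.4% | 40.5% |

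The 0.6 SD row is an illustrative smaller effect, not a protocol figure.

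**6. The labels against Table 2.**
- Continuous pain, all other items at maximum: 100 − 25 = 75, which is in the good band and a success. Such a patient can lose 75 − 60 = 15 further points and remain a success.
- Instability at each step, all other items at maximum: also 75.
- Baseline 20, 12 months 58: a gain of 38 points, labelled as no improvement or deterioration.
- Baseline 70, 12 months 61: a loss of 9 points, counted as a success. No entry criterion excludes a baseline of 70.

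**The case against.** **A 12-month success rate is a legitimate target.** It is easy to explain, and the outcome definition, sample size, chi-squared or Fisher test and logistic model all use it. This stands: the plan is coherent on the point, and the objection to the rate is one of efficiency and labelling.

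**A reader might infer that the cut throws away most of the score's information.** The documents do not support that. They give no Lysholm mean or SD, the two-thirds figure needs a normal model that strains against the ceiling at 100, and the skewed models put the loss at half or less.

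**A reader might infer that patients with continuous pain are generally counted as successes.** They are not. Using the options listed in Table 2, only 323 of 8,640 combinations of the other items (3.7%) reach 60 when pain scores 0. These are patterns, not probabilities, but the case is extreme. Pain is also measured separately by VAS at every visit. What stands is that the rule permits the label, and that the label then contradicts the sheet.

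**A reader might infer that Lysholm is excluded from score comparisons.** The list is introduced as examples, so it is open, and Lysholm at other visits is a secondary outcome without the efficiency formula. A score comparison is not ruled out; it is simply not the powered primary analysis.

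**A reader might infer bias from ignoring baseline.** Randomisation balances baseline in expectation, so the treatment comparison is not biased.

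**Binary power of 66–81% at 40 per arm is partly a sample-size matter.** This stands too, and that range should not be blamed on the cut alone.

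**Conclusion.** The point holds in a measured form. The primary outcome is the share scoring 60 or more at 12 months, without baseline, although the objective is framed in Lysholm scores. The cut costs a substantial part of the information: about 31–50% of the planned 42 per arm under the skewed models, and about two thirds under the equal-SD normal model. Both are assumptions, and the first range is the safer one to cite. In every scenario examined the score analysis needs fewer patients than the rate.

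Separately, and with no distributional assumption, the band labels can contradict Table 2 and describe change that a single total cannot show. The consequence is lost precision and a success label that is hard to interpret; the trial is not invalidated. The change is worth making because baseline and 12-month Lysholm scores are already collected.

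**What to change.** By amendment before unblinding:
- Make the primary analysis an ANCOVA of the 12-month Lysholm score on treatment and baseline Lysholm, reporting the mean difference with its 95% confidence interval.
- Keep the rate of 60 or more, with its 78% versus 97% basis, as a key secondary summary. Describe it as a state at 12 months, and remove the improvement and symptom-elimination wording from the bands.
- Restate the sample size justification for the score, giving the assumed SD and its source.

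No new visits, measurements or patients are needed. The cost is still more than wording. The trial is registered and recruiting, and Protocol amendments requires sponsor signature and ethics approval. The SD must be assumed or taken from pilot data that the article does not report. The headline becomes a mean difference in place of a success rate.

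If the sponsor prefers to keep the rate as primary, prespecify the baseline-adjusted score comparison as a supportive analysis, add baseline Lysholm to the logistic model, and still correct the band wording.

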#### Secondary outcome measures

Lysholm score at baseline, 3, 6, and 18 months after operationInternational Knee Documentation Committee (IKDC) score [23] at baseline, 3, 6, 12, and 18 months after operation. The IKDC scores range from 0–100 points and involves symptoms, sport activities, and function, with higher scores reflecting a better condition (knee function and symptoms)Visual Analog Scale (VAS) score [24] at baseline, 3, 6, 12, and 18 months after operation. The VAS is the most commonly used method to assess pain and consists of a 10-cm horizontal line with one end labeled as 0 cm representing “no pain” and the other end labeled as 10 cm representing “severe pain.” Patients will be instructed to make a mark on the line to indicate their pain intensity. The VAS scores range from 0–10 points, with 0 indicating no pain, 1–3 indicating mild pain, 4–6 indicating moderate pain, and 7–10 indicating severe painMRI examination to evaluate cartilage repair and regeneration at baseline, 3, 6, 12, and 18 months after operationAdverse events, such as fever, joint pain, swelling, effusion, and rejection after cartilage transplantation, will be observed at 3, 6, 12, and 18 months postoperatively. Common adverse events after microfractures include joint fever, joint pain, joint swelling, and effusion. All outcome evaluations will be performed independently and blindly by experienced evaluators

#### Adverse events

##### Safety

Standard operating procedures for adverse events and severe adverse events will be developed to ensure that any adverse reactions during the experiment will be treated quickly to protect the participants.

#### Definitions

##### Adverse events

Adverse medical events may occur after cartilage transplantation or microfracture surgery, but they do not necessarily have a causal relationship with treatment (Table 1).

**Table 1 Tab1:** Adverse event registration form

Adverse events		Appearance time	Duration
Fever	□		
Joint pain	□		
Joint snapping	□		
Joint noose	□		
Joint swelling	□		
Activity limitation	□		
Pruritus	□		

Common adverse reactions after cartilage transplantation include fever, joint pain, swelling, and effusion. Common adverse reactions after microfracture surgery include fever, joint pain, joint swelling, and effusion.

Adverse events will be relieved by nursing care, such as reducing activity, intermittent ice compress, and the use of non-steroidal anti-inflammatory analgesic drugs.

##### The severity of adverse events

Adverse events will be classified into three levels: general adverse events, vital adverse events, and severe adverse events.

##### Relationship with tissue-engineered cartilage

The correlation between adverse events and tissue-engineered cartilage will be categorized into “definitely related,” “probably related,” “possibly unrelated,” “irrelevant” or “undetermined.”

##### Severe adverse events

All events occurring during the trial requiring hospitalization or prolonged hospitalization, or resulting in disability, or affecting the ability to work, or with a risk of death or life-threatening events will be recorded.

#### Adverse event recording

All adverse events during the experiment will be collected until the end of the study.

#### Recording and reporting

All adverse events will be recorded by physicians, including description of adverse events, occurrence time, end time, severity, frequency, and treatment record.

Once a severe adverse event occurs, physicians will not only give necessary treatment, but also truthfully report to the local Food and Drug Administration Bureau and the National Food and Drug Administration Bureau within 24 h, as well as promptly report to the Ethics Committee. The data, treatment, and follow-up results will be noted in the report.

### Withdrawal criteria

Patients can withdraw from the study for any of the following reasons: severe adverse events (such as postoperative infections that are not eased within 1 week after surgery) related to the research; severe complications or rejection; the patient is asked to withdraw from the trial; considering the security or the benefit of the patient, the researchers believe that the patient is no longer suitable for continuing clinical validation; the patient fails to meet surgical requirements under arthroscopy; or is lost to follow-up. The time and cause of withdrawal will be recorded on an electronic Case Report Form (eCRF) in detail. When the study is discontinued, the patient should be assessed at the final visit except for those lost to follow-up. Free strategies for referral, physical examination, and MRI review will be conducted during the trial to improve patient compliance.

For patients who are out of the group and cannot be replaced or re-enter the clinical trial, their data will be treated as follows: (1) all source data and source files related to all withdrawn participants will be retained for retention and intent-to-treat analysis. After withdrawal, the researchers will attempt to contact the patient by telephone or mail to ask the reasons for withdrawal; (2) the time and cause of withdrawal will be recorded in the eCRF in detail; and (3) if there is judged to be a causal relationship with the trial, withdrawal due to adverse events will be recorded in the eCRF and the sponsor will be notified. For such patients, follow-up will be conducted until adverse events are resolved or stabilized.

### Data collection, management, and analysis

We will collect demographic data including the patient’s name, gender, date of birth, age, body weight, height, and Body Mass Index, will be recorded. The eCRF will be written in a unified format, clear and legible, including patient’s details, chief complaint, present illness history, past history, personal history, family history, physical examination, special examination, auxiliary examination, laboratory examination, final diagnosis, surgical records, and patient signature.

Two data clerks will input duplicate data into a computer database. The two separate sets of data will be compared by computer software, and modified according to the eCRF. Five percent of all case data will be randomly selected for manual checking. If the data error is greater than 0.15%, all the data in the database will be manually checked.

All participant data will maintain personal privacy. The full names of the subjects will not be present in records or documents. Only their abbreviated names will be displayed. Clinical trial data will include written data and electronic data. Electronic data will be stored in a specialized computer and managed by a data administrator using a password. Written data will be stored and locked in a fixed location, and the keys will be kept by an administrator.

### Data monitoring

An independent Data Monitoring Committee approved by the PLA General Hospital will be responsible for data monitoring, including protocol violations, recruitment rate, adverse events and participant compliance, and has the right to access all the trial data, but with no conflict of interest.

### Auditing

An inspector will audit the incoming data monthly and, if necessary, data queries will be raised. The inspector will review whether the eCRF is completed accurately. All discrepancies in the eCRF will be corrected by the researchers or authorized personnel in the appropriate manner.

### Sample size

Based on our previous experience [25] and pilot study results, we assumed that the therapeutic efficiency on full-thickness cartilage injury of the knee joint would be 78% for microfracture surgery and 97% for autologous, cell-derived, tissue-engineered cartilage transplantation. Considering *α* = 0.05 (two-sided), and power = 80%, the necessary sample size was calculated as *n* = 84. With a predicted dropout rate of 20%, the required sample size was calculated as *n* = 50 per group.

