### Study design

This prospective, single-blind, randomized controlled clinical trial will be conducted at the Institute of Orthopaedics, Chinese PLA General Hospital, China. The study design is compliant with the Standard Protocol Items: Recommendations for Interventional Trials (SPIRIT) Statement [20] (see Additional file 1). After providing informed consent, the potential patients with full-thickness cartilage injury of the knee joint will be screened according to the inclusion and exclusion criteria, and finally, 100 eligible patients will be randomly assigned to receive autologous-cell-derived tissue-engineered cartilage grafts (*n* = 50) or microfractures (*n* = 50). The primary outcome is therapeutic efficacy as assessed by the Lysholm score at 12 months postoperatively. The secondary outcomes are the IKDC score, Visual Analog Scale (VAS) score, and cartilage injury and repair as assessed by MRI as well as the incidence of postoperative adverse events (see the trial flow chart in Fig. 3). The Standard Protocol Items: Recommendations for Interventional Trials (SPIRIT) Figure is detailed in Fig. 4.

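### Randomising 50 per group does not preserve the protocol's own 84 patients after 20% dropout, and 84 matches no standard two-sided formula

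*Protocol article*

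**What the plan says.** The Sample size section assumes that the therapeutic efficiency "would be 78% for microfracture surgery and 97% for autologous"-cell tissue-engineered cartilage. With alpha "0.05 (two-sided), and power = 80"%, it gives 84 as the number needed. Since the enrolled number is 50 per group, 84 can only be a total, 42 per group. The next sentence reads "With a predicted dropout rate of 20%, the required sample size was calculated as" 50 per group. The Study design section confirms the enrolled total: "100 eligible patients will be randomly assigned to receive autologous-cell-derived tissue-engineered cartilage grafts" or microfracture, 50 in each arm.

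Efficiency is defined under Primary outcome measure as the share of patients whose Lysholm category is excellent or good, so the sample size rests on a binary outcome. The Statistical analysis section names two candidate tests, Fisher's exact and Pearson's chi-squared, and describes their role thus: "will be used for intergroup comparisons of categorical variables, such as curative outcomes and postoperative incidence of adverse events". The article gives no rule for choosing between the two. The same section plans an intention-to-treat full analysis set, with the last observation carried forward for patients lost to follow-up. No formula or software is named for the sample size.

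**The concern.** The paragraph makes two linked claims: that 84 patients give 80% power, and that 50 per group is enough to allow for 20% dropout. The second fails on the paragraph's own numbers. The first cannot be reproduced from the stated inputs by a standard two-sided formula.

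This paragraph is the article's only justification for the size of the trial. A null result on the primary comparison would be read against the stated 80%. If that figure belongs to a number of patients that the design does not expect to retain, or to a test other than the one used, readers will misjudge what the trial could detect.

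**Working it through.** **Inputs** (Sample size and Study design sections): p1 = 0.78, p2 = 0.97, difference d = 0.19, mean proportion 0.875, two-sided alpha 0.05 (z = 1.960), power 80% (z = 0.842), dropout 20%, 100 enrolled 1:1.

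**1. The dropout step**

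- Reproducing the plan's figure: 84 × (1 + 0.20) = 100.8 (42 × 1.2 = 50.4 per group). Rounded down, this is 50 per group.
- Correct allowance: 84/(1 − 0.20) = 105. Per group, 42/0.80 = 52.5, so 53, or 106 in total.
- Left after dropout from 100: 100 × 0.80 = 80, or 40 per group. This is 4 fewer than the stated 84.

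None of this depends on how 84 was obtained.

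**2. The figure of 84**

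The variance terms are 0.78 × 0.22 + 0.97 × 0.03 = 0.2007 (unpooled) and 2 × 0.875 × 0.125 = 0.21875 (pooled).

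- Unpooled: (1.960 + 0.842)² × 0.2007/0.19² = 43.6, so 44 per group, 88 in total.
- Pooled: (1.960 × √0.21875 + 0.842 × √0.2007)²/0.19² = 46.4, so 47 per group, 94 in total.
- Arcsine: h = 2·asin√0.97 − 2·asin√0.78 = 0.628; 2 × (1.960 + 0.842)²/h² = 39.8, so 40 per group, 80 in total.
- Pooled with continuity correction: 57 per group, 114 in total.
- Log odds ratio: 65 per group, 130 in total.
- Exact power of the uncorrected chi-squared test first reaches 80% at 39 per group, 78 in total.

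None gives 84. A one-sided arcsine calculation with continuity correction does give 42 per group, but the section states a two-sided alpha.

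**3. Power by method**

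The normal approximations come from the formulas above. For example, pooled at 40 per group: (0.19 × √40 − 1.960 × √0.21875)/√0.2007 = 0.636, so 73.8%. The exact figures enumerate both binomial distributions at 0.78 and 0.97.

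| Method | 40 per group | 42 per group | 50 per group |
|---|---|---|---|
| Normal, pooled | 73.8% | 75.9% | 83.0% |
| Normal, unpooled | 76.5% | 78.5% | 85.1% |
| Arcsine | 80.2% | 82.1% | 88.1% |
| Exact, uncorrected Pearson | 81.1% | 83.0% | 88.0% |
| Exact, Fisher | 65.8% | 69.5% | 77.4% |
| Exact, Pearson with Fisher if an expected count is below 5 | 70.5% | 74.3% | 85.6% |

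The last row uses a conventional switching rule that I have assumed, because the article states none. The rule matters here because failures are few. At 40 per group the expected number of failures is 40 × 0.22 + 40 × 0.03 = 10. An expected count falls below 5 whenever fewer than 10 failures occur in total, which happens in 44% of trials.

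**The case against.** **The trial analyses everyone.** With intention to treat and the last observation carried forward, all 100 stay in the analysis, and pooled power at 50 per group is 83.0%. This stands as a description of the planned analysis, and it means that a shortfall in power is not certain. But the 83.0% requires carried-forward values to show the full assumed 12-month effect. Those values would come from baseline, 3 or 6 months, and the withdrawal criteria include patients found unsuitable at arthroscopy. The Sample size section itself treats dropouts as lost, since it inflates for them.

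**84 may be adequate.** A reader might infer from 88 and 94 that 84 is too few. The documents do not support that. By arcsine or exact uncorrected Pearson, 84 is more than enough, and against the unpooled formula the gap is 2 per group. An arcsine size of 40 per group, correctly inflated, even gives 40/0.80 = 50 per group. That would make the enrolled number coherent, but the protocol says 84, not 80.

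**Power is below 80%.** A reader might also infer that power with 80 evaluable patients is in the low seventies under the planned test. The 73.8% belongs to the pooled approximation, and the 70.5% to a switching rule that the article does not state. Two methods in the table reach 80% at 40 per group.

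**An article condenses.** The full protocol or analysis plan may name the formula and the rule for choosing the test. That would settle where 84 came from. It would not remove the contradiction between 84, 20% and 50 per group, which are all printed.

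**Conclusion.** The dropout step is wrong as written, whatever formula lies behind it. With 20% loss, 100 enrolled patients leave 80, not 84, and keeping 84 would take 105 (106 with equal groups). The error is 5 to 6 patients in the inflation step.

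The figure of 84 is unexplained rather than shown to be too small: it matches none of the two-sided formulas tried but lies between the arcsine (80) and unpooled (88) results. Power with 40 evaluable per group runs from 65.8% to 81.1% depending on the method, so the stated 80% has no definite meaning until the formula and test are named. These figures assume the protocol's own 78% and 97%, equal loss in both groups, and dropouts that contribute nothing. The documents do not establish that the trial is underpowered or that more patients are needed.

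**What to change.** Keep N = 100 and correct the Sample size paragraph:

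- State the dropout allowance as n/(1 − 0.20), and remove the implication that 50 per group preserves 84 evaluable patients.
- Name the formula or software behind the calculation and the one primary test to which the power refers. If the test switches between Pearson and Fisher, give the rule.
- Restate the expected evaluable number as 80 (40 per group) with its power under that test: for example 70.5% if Fisher replaces Pearson whenever an expected count is below 5, or 73.8% by the pooled formula.
- If power is also quoted for all 100 patients, say that it assumes carried-forward scores show the full 12-month effect.

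Possible wording: *With 50 patients randomised per group and 20% dropout, 40 per group are expected to be evaluable at 12 months. For 78% against 97% at two-sided alpha 0.05, this gives power of [value] by [named method and test].*

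This changes wording only. The one downside is that the stated power becomes less favourable under most of the methods above.
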